**Sample Size Considerations**

Presentation of sample size is based on achieving 80% power overall to demonstrate that improvement rate in *NIHSS test score* is at least 0.25 and, separately, that improvement rate in *ADL test score* is at least 0.25. An improvement rate of at least 25% in the NIHSS test and ADL score in the treatment group (comparing to baseline, prior to HBOT treatment) would be an appropriate clinical target for HBOT treatment success and of sufficient interest to encourage further investigation of HBOT treatment for post stroke patients suffering chronic NIHSS deficiencies.

Sample size was based on the assumption that exposure to the NIHSS tests and ADL evaluation (at baseline) without any additional training might induce up to 4% score improvement in the second NIHSS test (following treatment). Assuming a true success rate of 25% a sample of N = 31 will provide 80% power to show that HBOT treatment induces at least 25% improvement on *NIHSS test score* and separately, on *ADL test score*. This is based on a power analysis using the normal approximation for the binomial, with one-sided Alpha=0.05.

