### Primary Efficacy Analysis

This study has co-primary endpoints: *NIHSS tests score* and *ADL score.* For each of the co-primary endpoints we will compute Overall Proportion of Success:

The following hypotheses are specified and will be tested separately:

For *NIHSS tests score* proportion of improvement:

H_0_: p_1_< p _2_

H_1_: p _1_> p _2_

While p1= 0.25 and p2=0.04

For *ADL score* proportion of improvement:

H_0_: p_1_< p _2_

H_1_: p _1_> p _2_

While p1= 0.25 and p2=0.04

Each of these hypotheses will be tested by:

1. Constructing a one-sided, lower 95% confidence interval about the observed Overall Proportion of Success in the relevant cohort.
2. Examining whether the lower limit of the confidence interval is at or above the success criterion

Study success will be declared if the following is met:

1. Lower confidence limit of HBOT treatment success is at 0.25 or above

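### The 80% power at one-sided 5% with N = 31 comes from a normal approximation with only 1.24 successes expected under the null; the figures should be exact and tied to a named limit

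*Protocol*

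**What the plan says.** Protocol, Sample Size Considerations, gives the planning claim: "Assuming a true success rate of 25% a sample of N = 31 will provide 80% power". It names the method in the next sentence: "This is based on a power analysis using the normal approximation for the binomial, with one-sided Alpha=0.05".

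Protocol, Primary Efficacy Analysis, supplies the two rates for each co-primary endpoint (NIHSS and ADL): "While p1= 0.25 and p2=0.04". Each hypothesis is to be tested by "Constructing a one-sided, lower 95% confidence interval about the observed Overall Proportion of Success in the relevant cohort". The section does not say how that limit is calculated. The closing criterion for study success is: "Lower confidence limit of HBOT treatment success is at 0.25 or above".

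The normal approximation is therefore stated for the power analysis only. It is also the only binomial method the protocol names.

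**The concern.** A normal approximation to the binomial needs a reasonable number of expected events at the rate being tested. Here the null rate is 4% and the sample is 31, so little more than one success is expected if the null is true. The distribution of the count is then strongly skewed and coarse. An alpha and a power taken from the normal curve need not match what the decision rule delivers.

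The lower confidence limit decides whether the trial succeeds. If the stated 5% and 80% do not belong to any rule the trial could apply, the reader cannot tell how many successes are required, what false-positive risk is accepted, or whether 31 is more or fewer patients than needed.

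**Working it through.** **Inputs.** n = 31, one-sided alpha 0.05 and power 80% come from Sample Size Considerations. The null rate 0.04 and alternative 0.25 come from Primary Efficacy Analysis. Two assumptions are needed. First, 31 is taken as the number entering one proportion, because the protocol does not say whether it is per arm or in total. Second, 4% is taken as a proportion of successes, as the hypotheses use it, although Sample Size Considerations words it as a score improvement.

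**Step 1: reproduce N = 31.** Take the one-sample normal formula with the variance at the alternative:

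n = (1.645 + 0.842)² x 0.25 x 0.75 / (0.25 - 0.04)² = 26.3

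With continuity correction:

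n = (26.3 / 4) x [1 + √(1 + 2 / (26.3 x 0.21))]² = 30.9, rounded up to 31

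The planned power at 31 by this route is 80.2%. The stated figure can thus be reached by a continuity-corrected Wald calculation, though the protocol does not state its formula. With the null variance for alpha and the alternative variance for power, the same one-sample normal approach gives 10.7, or 15.1 corrected. A spread from about 11 to 31 from variants of one approximation is itself a sign that it is unreliable here.

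**Step 2: expected null count.** 31 x 0.04 = 1.24.

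**Step 3: exact behaviour against 0.04.** For each kind of lower 95% limit, find the smallest count r whose limit reaches 0.04. Then compute P(X ≥ r) for X ~ Binomial(31, p).

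| Limit | Limit at r - 1 | Limit at r | Rule | True error (p = 0.04) | Power (p = 0.25) |
|---|---|---|---|---|---|
| Clopper-Pearson | 0.0269 | 0.0453 | ≥ 4/31 | 3.40% | 96.9% |
| Wilson | 0.0393 | 0.0593 | ≥ 4/31 | 3.40% | 96.9% |
| Wald | 0.0300 | 0.0526 | ≥ 5/31 | 0.73% | 91.7% |
| Wald, continuity-corrected | 0.0365 | 0.0607 | ≥ 6/31 | 0.13% | 82.4% |

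None of these rules has an error near 5%. For the continuity-corrected Wald rule, the one that reproduces N = 31, the stated power is close (80% planned, 82.4% true), but the true alpha is 0.13%. For an exact test against 0.04, 80% power is first reached at n = 16 (at least 3 successes, error 2.4%, power 80.3%).

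**Step 4: behaviour at the written bar of 0.25.** The expected count at that bar is 31 x 0.25 = 7.75.

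| Limit | Rule | Probability of success at p = 0.25 |
|---|---|---|
| Clopper-Pearson | ≥ 13/31 (limit 0.2688) | 2.89% |
| Wald, with or without correction | ≥ 13/31 (limit 0.2736, or 0.2574 corrected) | 2.89% |
| Wilson | ≥ 12/31 (limit 0.2579) | 6.44% |

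Here Wald and exact limits give the same rule. Wilson exceeds the nominal 5%.

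**The case against.** The strongest reply has four parts.

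1. The sentence about the normal approximation describes the power analysis. The protocol never says that the confidence limit is Wald, and interval construction is often left to the analysis plan. This stands. A reader might infer that the trial's limit is a Wald limit with a 0.7% error, but the protocol does not establish that, so the Wald rows above are conditional. What remains is the stated power and alpha, which the protocol itself ties to the approximation.

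2. The departure is harmless in direction. This also stands. A reader might take an error rate far from 5% to mean too many false positives, or a trial too small for the 4% comparison. Neither follows: every rule in Step 3 has an error below 5% and power above 80%. Part of the gap to 5% is discreteness, which the exact limit shares (3.4%).

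3. The written success criterion uses 0.25, not 0.04. At 0.25 the small-count argument does not apply, and moving from Wald to exact changes nothing. This is correct. The choice of limit still matters there in one respect: 12/31 passes under Wilson and fails under Wald or Clopper-Pearson.

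4. A reader might recast the problem as a comparison of the two randomised arms and ask whether 31 per arm gives 80% power. Primary Efficacy Analysis specifies a limit on one observed proportion against fixed values, with no test between arms. Power for such a test is therefore not evidence on this point.

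**Conclusion.** The point holds in a limited form. With 1.24 successes expected under the null, the normal approximation is a poor basis for the planning figures. The stated pair of 80% power and 5% one-sided alpha does not describe an exact test of 25% against 4% at n = 31, which has 96.9% power and 3.4% error. If the unnamed limit were Wald, the true error would be 0.7%, or 0.13% with continuity correction.

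The consequence is a misstated operating characteristic in the conservative direction. It does not show that inference is invalid or that power against 0.04 is lost. The conclusion assumes that 31 enters a single proportion and that 4% is a success rate.

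The larger difficulty lies beside this one. The null is 0.04 but the success bar is 0.25, and under the written bar a true rate of 25% meets the criterion only 2.9% of the time with a Wald or exact limit. That inconsistency is separate, and changing the approximation does not cure it. It must be reconciled first, because no power figure has meaning until the bar is fixed.

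**What to change.** 1. **Settle the bar.** Decide whether the lower limit is to be compared with 0.04 or with 0.25, and make the hypotheses and the success criterion agree.

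2. **Sample Size Considerations.** Replace the normal approximation with exact binomial enumeration. State the number of successes required, the true alpha and the power for the rule adopted, and say whether 31 is per arm or in total. If the bar is 0.04 and 31 enter the proportion, the entry is: at least 4/31, true one-sided error 3.4%, power 96.9% at 25%. If the bar is 0.25, the entry is: at least 13/31, error 2.9% at 25%. Power then has to be computed at an assumed rate above 25%, which the protocol does not give.

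3. **Primary Efficacy Analysis.** Name a one-sided 95% Clopper-Pearson lower limit. Do not substitute Wilson: it matches the exact rule at 0.04, but at the written bar of 0.25 it passes at 12/31 with 6.4% error.

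Apart from settling the bar, the cost is about one sentence in each section and one recalculated figure. The downside is that the exact limit is slightly conservative, with 3.4% error at 0.04 or 2.9% at 0.25 against the nominal 5%.

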## Statistical Analysis

### Safety Analysis

AE's will be tabulated by treatment group, severity and relation to treatment.

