***Study protocol***

After signing the informed consent, patients were randomized in 1:1 manner into the treated or the control-cross group. After the randomization, patients were invited for baseline evaluation that included full review of their medical status and complete physical examination. All patients had baseline CT scan. After their inclusion patients were randomized to two groups: a treated group and a cross group. All patients had evaluation of their neurologic functions by physical examination, ability to perform activities of daily living, quality of life and brain functional imaging (rCBF-SPECT scan). The patients in the treated group were evaluated twice – at baseline and after 2 months of HBOT treatment. The patients of the cross group were evaluated three times – at baseline, after a 2 month control period of no treatment and after a consequent 2 month period of HBOT treatment. We emphasize that the study was a cross-over trial and patients in the cross group received HBOT treatment after their second evaluation and had a third neurological evaluation after the cross, when they have completed their HBOT.

The following HBOT treatment protocol was practice: The patient were treated 40 times (each treatment session was given on a separate day) distributed over two months (five days a week). Each session was for 90 minutes in 100% oxygen atmosphere and at pressure of 2 ATA.

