**Randomization**

Since the diversity of the patients included in the study, after signing the informed consent was expected to be high, no stratifies criteria was used. Patients were randomized in 1:1 fashion to either treatment or controlled-cross group.

There is no placebo in the cross group during the control period. The only way to give “placebo” of HBOT, is to bring the patients to the hyperbaric chamber and to increase the environmental pressure- in a way the patients will “feel the hyperbaric pressure” in their ears. However, Henry’s law states: “the amount of a given gas dissolved in a given type and volume of liquid is directly proportional to the pressure of that gas in equilibrium with that liquid”. Thus, hyperbaric environment significantly increases the dissolved oxygen pressure even if a person holding his breath[^76^](#_ENREF_76). Moreover, the alternative of hosting the patients in the hyperbaric chamber without any pressure increase cannot serve as a real placebo since the patients will not feel the pressure. Accordingly, the only real “placebo” could be archived by increasing the pressure and reducing the percentages of the oxygen but that holds significant safety consideration.

From the ethical point of view, it was deemed unethical to “treat” the patients (40 sessions in the hyperbaric chamber) while they actually know that it is a placebo. In order to somewhat compensate for this limitation, the control was a cross group and after the 2^nd^ evaluation at the end of a control period they were crossed to HBOT. The cross for treatment enables intra-group efficacy evaluation in both treatment and control group.

Since the patients knew they were not receiving HBOT during the control period they were not blinded with regard to the treatment arm. Accordingly the ADL and quality of life evaluations were not blinded. Moreover, in the current clinical setting, it was not possible to assure that the NIHSS evaluation could be done completely blinded by the physician. The complete blindness evaluation could be assured in the brain SPECT evaluation done by the radiologist. The correlation between metabolic blinded evaluation of the brain (SPECT) and the neurological un-blinded evaluations give further support and strength to the clinical findings.

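### The adverse event table can mix opportunity for detection with risk: 40 attendances on HBOT, no stated contact during the control period, and no common way of eliciting events

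*Protocol*

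**What the plan says.** Safety Analysis consists of one sentence: "AE's will be tabulated by treatment group, severity and relation to treatment". It does not mention periods or time at risk.

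Study protocol fixes the contacts. For HBOT: "The patient were treated 40 times (each treatment session was given on a separate day) distributed over two months (five days a week"). For the treated group: "The patients in the treated group were evaluated twice – at baseline and after 2 months of HBOT treatment". The cross group is evaluated "at baseline, after a 2 month control period of no treatment and after a consequent 2 month period of HBOT treatment", and no visit or call is stated between the first two of those evaluations. Both groups reach HBOT in the end, since "patients in the cross group received HBOT treatment after their second evaluation".

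Randomization adds that "There is no placebo in the cross group during the control period", so control patients make no matching attendances. It also says of the patients that "they were not blinded with regard to the treatment arm".

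Adverse Events asks for every event that starts between the screening visit and the patient's final study day, which takes in the control period. Assessment of Adverse Events has the investigator assess each event and enter it on the case report form with its dates. Neither section says when or how patients are to be asked, on HBOT or off it. The Safety Analysis Set is everyone who started study treatment. It selects patients, not periods, so control-period events of cross patients who later start HBOT stay in.

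**The concern.** A patient who is in the hyperbaric unit five days a week has many occasions on which a brief or minor complaint can be mentioned or seen. A patient who is next seen after two months has one, and depends on memory. If the table sets these two kinds of time side by side, a higher count on HBOT may reflect more events, more complete recording, or both, and nothing in the table separates them.

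Matching the length of follow-up does not remove the problem, because it is present when two months of HBOT are compared with two months of control. Serious events are less exposed, since they are less likely to be missed or forgotten. What is at stake is the reading of mild, transient events. Safety in this population is a stated aim under Objectives, and the control period offers the trial's only untreated AE data.

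**Working it through.** **Inputs from the protocol**

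- HBOT sessions: 40, five a week (Study protocol). Check: 40 / 5 = 8 weeks, which agrees with the stated two months.
- Evaluations: treated group at baseline and 2 months; cross group at baseline, 2 months and 4 months (Study protocol; Neurologic evaluation).
- Sham attendances in the control period: none (Randomization).
- AE recording: both periods (Adverse Events).

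**Stated contacts after baseline up to the 2-month evaluation**

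- Treated group: 40 sessions + 1 evaluation = 41.
- Cross group: 0 sessions + 1 evaluation = 1.

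These are counts of contacts. They do not convert into a ratio of detection probabilities.

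**Assumed inputs**

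The protocol gives no capture probabilities. Assume that a fraction d_H = 0.95 of events is recorded on HBOT and d_C = 0.95, 0.8, 0.5 or 0.3 in the control period. The first value is equal capture, that is, no bias. Assume also the same true event rate in every two-month period.

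**Formulas**

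Recorded events = true events × capture, so the true rate cancels.

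- Reading A, HBOT against control time (by period, or by randomised group up to month 2): ratio = d_H / d_C.
- Reading B, randomised groups over all follow-up: treated patients have 2 months of HBOT; cross patients have 2 months of control plus 2 months of HBOT. Events per patient, treated/cross = d_H / (d_C + d_H). Events per month = (d_H / 2) / ((d_C + d_H) / 4) = 2 d_H / (d_C + d_H).
- Reading C, events on HBOT only: both groups have 40 sessions, so the ratio is d_H / d_H = 1, but there is no control column.

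**Results with equal true rates**

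| d_C | A: 0.95 / d_C | B, per patient: 0.95 / (d_C + 0.95) | B, per month: 1.90 / (d_C + 0.95) |
|---|---|---|---|
| 0.95 | 1.00 | 0.95 / 1.90 = 0.50 | 1.00 |
| 0.80 | 1.19 | 0.95 / 1.75 = 0.54 | 1.09 |
| 0.50 | 1.90 | 0.95 / 1.45 = 0.66 | 1.31 |
| 0.30 | 3.17 | 0.95 / 1.25 = 0.76 | 1.52 |

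Under A the detection effect appears in full. Under B per month it is diluted, because the cross group's HBOT time is captured as well as the treated group's. Under B per patient the ratio is below 1 throughout, because cross patients are followed for 4 months against 2. Unequal follow-up dominates there, and the detection effect moves the ratio from 0.50 towards 1. Under C there is no detection difference and no comparison with control.

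**The case against.** The strongest reply has four parts.

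1. *The protocol does not say that events are noted at sessions.* A reader might infer that AEs are collected at each of the 40 sessions on HBOT and only at the end of the control period. The text supports neither statement: it sets no collection times at all. This stands. What the protocol does establish is a large difference in opportunity and no common procedure to offset it.

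2. *The table is by group, not by period.* A reader might take the treatment-group columns to mean HBOT against control time. Safety Analysis does not say so. Study protocol names a treated and a cross group, and both receive 40 sessions. This stands too, and it is why the effect is full on one reading and diluted on another. It would vanish only if the table were limited to events on HBOT, a limit the text does not state.

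3. *The aim is descriptive.* Objectives asks that safety be evaluated and events recorded; there is no safety hypothesis, test or success criterion. It would therefore be too strong to say that the safety objective goes unanswered for non-serious events. The table can still describe tolerability on HBOT. The point concerns only its use as a contrast with control.

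4. *Such detail belongs in an analysis plan or in form instructions.* For table layout this is fair. It fails for elicitation: an analysis plan can split events by onset date, but it cannot recover control-period events that nobody asked about.

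The absence of a sham is a choice that Randomization explains, and it is not criticised here.

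**Conclusion.** The point holds in limited form. The stated schedule gives 40 attendances in two months on HBOT and no stated contact in the control period before its closing evaluation. AEs from both periods are to be recorded, no common elicitation is set, and the only tabulation is by an undefined treatment group. Any part of that table that sets HBOT time against control time mixes detection with risk, most likely to HBOT's disadvantage for mild, short-lived events.

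The size is unknown. The by-period ratios of 1.0 to 3.2 rest wholly on assumed capture rates and equal true rates, and they include the case of no bias. A reader might take 41 contacts against 1 as a measure of the bias, or conclude that HBOT must show a raised AE count. Neither follows: contacts are not capture probabilities, and by randomised group over all follow-up the per-patient ratio falls below 1 because of the 2 against 4 months of follow-up.

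**What to change.** - At the existing evaluation that ends each two-month period, ask every patient the same structured AE questions about that period.
- Add a source flag to the AE page: elicited at an evaluation, or noted at an HBOT session.
- Tabulate AEs by period (control or HBOT), and say so in Safety Analysis.
- Show any HBOT-versus-control contrast for serious events and evaluation-elicited events.
- Report all AEs on HBOT, including those noted only at sessions, as on-treatment tolerability, and do not read them as a comparison with control.

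The cost is one question set at visits already planned, one field on the form and a revised table; no visit is added and treatment is unchanged. The drawback is that the contrast rests on two-month recall by unblinded patients and holds fewer mild events. Patients who reported an event at a session may also recall it more readily. The change therefore narrows the difference in ascertainment without removing it, and the report should say so.

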**Statistical Considerations**

## Analysis Sets

### Safety Analysis Set

The safety analysis set will consist of all subjects for whom the study treatment was initiated.

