**Adverse Events**

An adverse event (AE) is any untoward medical occurrence in a clinical investigation subject administered a medicinal product and which does not necessarily have a causal relationship with this treatment. An AE can therefore be any unfavorable and unintended sign, symptom, or disease temporally associated with the use of a medicinal product, whether or not considered related to the medicinal product. Pre-existing events, which increase in severity or change in nature during or as a consequence of use of a medicinal product in human clinical trials, will also be considered AEs.

Any medical condition or clinically significant laboratory abnormality with an onset date before the screening visit and not related to study procedures is considered to be pre-existing, and should be documented in the case report form.

Any AE (i.e., a new event or an exacerbation of a pre-existing condition) with an onset date after the screening visit up to the last day on study (including the follow-up, off study medication period of the study), should be recorded as an AE on the appropriate CRF page(s).

An AE does not include:

- Medical or surgical procedures (e.g. surgery, Endoscopy, tooth extraction, transfusion); the condition that leads to the procedure are an adverse event.
- Pre-existing diseases or conditions or laboratory abnormalities present or detected prior to the screening visit that does not worsen.
- Situations where an untoward medical occurrence has not occurred (e.g. hospitalization for elective surgery, social and/or convenience admissions).
- Overdose of either study drug or concomitant medication without any signs or symptoms unless the subject is hospitalized for observation.

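### Tabulating adverse events by treatment group mixes HBOT and untreated time over unequal follow-up, so all-cause counts by arm cannot contrast HBOT with no treatment

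*Protocol*

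**What the plan says.** The Safety Analysis section of the protocol is one sentence: "AE's will be tabulated by treatment group, severity and relation to treatment". The analysis set is defined just as briefly: "The safety analysis set will consist of all subjects for whom the study treatment was initiated".

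The Randomization section names the groups: "Patients were randomized in 1:1 fashion to either treatment or controlled-cross group". The Study protocol section sets their follow-up. For the treated arm: "The patients in the treated group were evaluated twice – at baseline and after 2 months of HBOT treatment". The cross arm is evaluated three times: "at baseline, after a 2 month control period of no treatment and after a consequent 2 month period of HBOT treatment". It also confirms that "patients in the cross group received HBOT treatment after their second evaluation".

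The Adverse Events section asks for every event "with an onset date after the screening visit up to the last day on study" to be recorded, and it expressly counts time off study medication. The Assessment of Adverse Events section requires dates of onset and resolution and a yes/no judgement of relation to study drug or study procedures. The Objectives section makes the safety of HBOT in these patients something the trial will evaluate.

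Nowhere does the protocol assign events to a period, separate the control period from the later HBOT period of the cross arm, or give a denominator in exposure time.

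**The concern.** A two-column table by arm usually sets exposed patients against unexposed patients. Here it cannot. The treated column holds HBOT time only. The cross column holds the same planned HBOT time plus an untreated period of equal length. The difference between the columns then mainly reflects the extra 2 months of observation in the cross arm, not the effect of HBOT.

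At stake is the safety objective. The control period is the only concurrent information on how often these patients have events without HBOT, and the stated table merges it with HBOT time. Someone who takes the cross column for the control would see fewer events with treatment, whether or not HBOT causes harm.

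A second, smaller matter is the safety set. A cross patient enters it only by starting HBOT. One who dies or withdraws in the control period is left out, together with events that the protocol requires to be recorded.

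**Working it through.** The protocol gives no figure to reproduce here: it states no event rates and no expected dropout. The check uses the planned follow-up and assumed rates.

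**Inputs**
- Follow-up (Study protocol section): treated arm 2 months on HBOT; cross arm 2 months untreated, then 2 months on HBOT.
- Allocation 1:1 (Randomization section).
- Assumed: constant monthly event rates *c* untreated and *h* on HBOT; *c* from 0.02 to 0.10; true rate ratio *r* = *h*/*c* from 1 to 3.
- Assumed for counts only: *n* = 31 per arm. The Sample Size Considerations section gives 31 without saying whether this is per arm or in total. The ratios below do not depend on *n*.

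**Step 1: expected event counts by arm, no dropout**

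Treated: *n* × 2*h*. Cross: *n* × (2*c* + 2*h*). Their ratio is *h*/(*c* + *h*) = *r*/(1 + *r*), which is below 1 whenever *c* > 0. It is 0.50, 0.60, 0.67 and 0.75 at *r* = 1, 1.5, 2 and 3. With *c* = 0.05 and *n* = 31, the counts are 3.1 vs 6.2 (*r* = 1), 6.2 vs 9.3 (*r* = 2) and 9.3 vs 12.4 (*r* = 3). The direction does not depend on the assumed rates.

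**Step 2: share of patients with at least one event**

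The share is 1 − exp(−rate × time). For *c* = 0.05 and *h* = 0.10:
- treated arm: 1 − exp(−2 × 0.10) = 18.1%
- cross arm: 1 − exp(−2 × 0.05 − 2 × 0.10) = 25.9%
- control period alone: 1 − exp(−2 × 0.05) = 9.5%

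By arm the table reads 18.1% vs 25.9%. By period it reads 18.1% on HBOT vs 9.5% untreated. Over the assumed range:

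| *c* per month | *r* | Treated arm (also the HBOT period) | Cross arm | Control period |
|---|---|---|---|---|
| 0.02 | 1 | 3.9% | 7.7% | 3.9% |
| 0.02 | 2 | 7.7% | 11.3% | 3.9% |
| 0.02 | 3 | 11.3% | 14.8% | 3.9% |
| 0.05 | 1 | 9.5% | 18.1% | 9.5% |
| 0.05 | 2 | 18.1% | 25.9% | 9.5% |
| 0.05 | 3 | 25.9% | 33.0% | 9.5% |
| 0.10 | 1 | 18.1% | 33.0% | 18.1% |
| 0.10 | 2 | 33.0% | 45.1% | 18.1% |
| 0.10 | 3 | 45.1% | 55.1% | 18.1% |

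In every row the treated arm is lower than the cross arm, including the rows with no HBOT effect (*r* = 1).

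**Step 3: is a person-time denominator enough?**

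No. The cross arm's rate per patient-month is (*c* + *h*)/2. At *c* = 0.05 and *h* = 0.10 this is 0.075, so the ratio by arm is 0.10/0.075 = 1.33 where the true ratio is 2. Events have to be split by period as well.

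**Step 4: effect of the treatment-initiated set**

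Suppose a fraction *d* of cross patients leaves before HBOT and is excluded, and the rest have unchanged rates. The cross count becomes *n*(1 − *d*)(2*c* + 2*h*), which moves it down, against the direction in step 1. With *c* = 0.05 and *d* = 20%, the counts are 6.2 vs 7.4 at *r* = 2 and 9.3 vs 9.9 at *r* = 3, so the treated arm is still lower. The order changes only when *d* exceeds 1/(1 + *r*): 50%, 33% and 25% at *r* = 1, 2 and 3.

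**The case against.** The strongest objection is that this is one sentence about a descriptive table, and that periods and denominators belong in an SAP, which is not at hand. Event dates are recorded, so nothing prevents a period-based table. That would answer a complaint about silence. But the protocol does state both a grouping and an analysis set, and an SAP that follows them inherits the problem.

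A second objection is that treatment group is not defined for this table and could mean treatment received. That is possible. The Randomization and Sample Size Considerations sections point to the arm, so it is the natural reading though not the only one. Under the other reading the wording would need to say so, and the safety set would still lose non-starters.

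A third objection is that the table is also split by relation to treatment. A control-period event cannot be related to HBOT that has not been given, and in HBOT-related rows both arms contribute the same planned 2 months. Much of this stands: the imbalance in steps 1 and 2 concerns all-cause counts. But attribution is an investigator's judgement in a trial where patients know their treatment and the protocol concedes that even the NIHSS assessment may not be blinded. It also covers study procedures, and it yields no untreated background rate.

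A reader might infer that the planned table will present HBOT as safer than no treatment, or will reverse a real harm. The document does not support that. It labels no column as untreated and sets no comparative safety hypothesis or decision rule. The reversal arises only when all-cause counts are read with the cross column as the control. A reader might also infer that the safety set adds to the same bias. It does not: it loses only patients who never start HBOT, possibly none, and works in the opposite direction.

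**Conclusion.** The point holds for all-cause events, on the natural reading of treatment group as randomised arm. The stated table compares about 2 months of HBOT with about 4 months of mixed exposure, so it cannot contrast HBOT with no treatment. Without dropout, the expected treated-to-cross count ratio is one half when HBOT has no effect and stays below 1 for any rate increase. That result rests on equal arms, follow-up as planned and a non-zero untreated rate. The percentages are illustrations under assumed constant rates and say nothing about the rates in this trial. The relatedness split reduces the problem but does not remove it.

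The loss of control-period events in cross patients who never start HBOT is a separate, smaller defect of unknown size. This should be corrected before the safety tables are produced. It does not affect the efficacy analysis.

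**What to change.** Replace the Safety Analysis sentence with a rule based on exposure at onset:
- Tabulate events in the HBOT period (pooled and by arm) against the control period of the cross arm, keeping severity and relation to treatment as further splits. Give patients at risk and person-time for each column.
- Show the first 2 months by randomised arm as the concurrent comparison, since only there do the arms have equal time and distinct exposure.
- Keep the treatment-initiated set for HBOT-period events. For the control period, and for the first-2-months comparison, include all randomised patients with any post-baseline observation.
- Define treatment group wherever the term remains in the safety text.

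The cost is wording in the protocol or SAP and a period flag derived from event onset dates, which are already required, and the date of the first HBOT session. No new visits or assessments are needed.
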